## **Data monitoring**

Data monitoring is being undertaken throughout the trial, based on a data monitoring and auditing plan (DMAP) devised by the study team. The DMAP was developed in accordance with the ICH E6 (R2) Good Clinical Practice Guideline (17) and reflects current best practice for data monitoring practices in investigator-initiated trials. Briefly, the DMAP includes the following components:

- Data verification on all screening data items (i.e. inclusion and exclusion criteria) on a random sample of 20 ineligible patients (or all patients if less than 20 ineligible patients) from each site;
- Data verification on all screening data items (i.e. inclusion and exclusion criteria) for every enrolled patient;
- Data verification on the stratification used for randomisation and consent data items and data items related to calculation of the primary outcome and secondary outcomes for every enrolled patient; and
- Data verification on key data items relating to cohort descriptors on a random sample of 10% of enrolled patients from each site.

The original study REDCap database was enhanced to facilitate the DMAP. Each Australian and New Zealand site is being monitored by a research co-ordinator from a different trial site. This is being undertaken through a combination of on-site monitoring and remote monitoring using the institutional programme to share desktop computer screens. All sites except one have the required information for physiological data, treatment, outcomes, laboratory values, and patient notes on an electronic health record. One site has parts of the patient data on paper, which requires digital scanning for review. During the coronavirus-2019 pandemic (COVID-19), sites are only allowing remote monitoring. Each relevant data item is verified individually by comparing the entered value with the value in the source documentation. Where

discrepancies are found, the site research co-ordinator and monitor meet to discuss and resolve the discrepancies. Once data monitoring is finalised, the patient's REDCap data entry record is locked in preparation for analysis. The site in The Netherlands is being monitored onsite by an external monitoring company as remote monitoring is not permitted in The Netherlands; during the COVID-19 pandemic, monitoring was paused.

## **Statistical analysis**

### *Statistical analysis principles*

- Analyses will be conducted based on the intention-to-treat principle. Specifically, patients who are eligible, who do not meet any exclusion criteria and who undergo randomisation will be analysed based on the treatment group they were allocated to, independent of the compliance with the treatment delivered.
- Participants who had more than one surgery before their second birthday will only have data related to their first surgery for which study consent was available analysed.
- Statistical tests will be two-sided applying a statistical significance level of 0.05. As we are not correcting for multiplicity when comparing secondary or other outcomes, such results will be considered exploratory and will be reported as point estimates with 95% confidence intervals (CIs).
- If there is missing data for the primary outcome measure for any participants, imputation methods will be used.
- Continuous variables will be assessed for normality; this will be undertaken using visual inspection of histograms and Q-Q plots.
- Standard descriptive statistics will be used when summarising variables; frequencies (percentages) for discrete variables, mean and standard deviation (SD) for continuous

variables, or, if continuous variables are non-normally distributed, median with interquartile range (IQR).

- This analysis plan and the primary manuscript will only include analyses up to 28 days. We will present analyses of postoperative delirium, health care costs, inflammatory markers and long-term outcomes (12 months and later post procedure) separately.
- Pre-planned subgroup analyses will be performed including the pre-defined study strata; these will be executed regardless of any potential treatment effect on the primary or secondary outcomes in the main cohort.
- To ensure transparency and reproducibility, the Stata code that will be used to analyse the final study data is available on GitHub (16).
- The trial statistician will be blinded to the treatment group until the analyses outlined in this SAP have been completed.
- Changes in the analysis plan by the investigators effective after publication of this SAP will be declared as such.

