#### 5.1.2 Exclusion criteria

- Signs of persistently elevated pulmonary vascular resistance preoperatively requiring iNO or preoperative intravenous use of drugs involved in the NO pathway such as GTN, within 48 hours prior to CPB (oral sildenafil treatment alone is not an exclusion).
- Patient is on ECLS immediately prior to surgery

- Chronic ventilator dependency
- Concurrent known confirmed bacterial sepsis/septic shock, diagnosed within <48 hours prior to surgery and being actively treated with antibiotics at time of surgery (suspected sepsis treated with antibiotics is not an exclusion criteria unless inotropes are required for treatment of septic shock at time of surgery)
- Preoperative acute respiratory distress syndrome requiring HFOV ventilation <48 hours of surgery
- Patient requires high doses of vasoactive drugs prior to surgery with an inotrope score  $\geq 15$  met within 24 hours prior to surgery: Inotrope requirement will be calculated by means of the Vasoactive-Inotrope Score (VIS) (2):  $VIS = \text{dopamine dose (mcg/kg/min)} + \text{dobutamine dose (mcg/kg/min)} + 100 \times \text{adrenaline dose (mcg/kg/min)} + 100 \times \text{noradrenaline dose (mcg/kg/min)} + 10 \times \text{milrinone dose (mcg/kg/min)} + 10,000 \times \text{vasopressin dose (U/kg/min)}$ .
- Cardiac arrest within one week (7d) prior to surgery
- Emergency cardiac surgery which may preclude obtaining informed consent (defined as acutely required life-saving procedure in a patient unlikely to survive the next hours without the surgery)
- Pre-existing methaemoglobinemia (MetHb > 3%)

NB. Patients that were previously enrolled and randomised into the study with surgical procedure performed that required use of cardio-pulmonary bypass will not get re-randomised. Previously enrolled and randomised patients will undergo the same treatment allocation for subsequent surgeries, unless parents opt out. Rationale: For patients undergoing same procedures, any potentially additive protective impact of NO during CPB on long-term neurodevelopment may become diluted by use of CPB without NO during subsequent procedures. We expect that ca. 10% of all CPB cases <2 years may require subsequent CPB <2 years of age.

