## 8 ADVERSE EVENTS AND RISKS

### 8.1 Definitions

Adverse Event (AE) is any untoward medical occurrence in a patient enrolled into this study regardless of its causal relationship to study treatment intraoperatively and ***within the first 48 hours postoperatively.***

Serious Adverse Event (SAE) is any AE that results in:

- Death
- Is life-threatening
- Requires prolongation of existing hospitalisation
- Results in persistent or significant disability/incapacity
- Requires intervention to prevent permanent impairment or damage

**Specific AEs related to NO delivery during CBP: air embolism, severe hypotension during bypass and increased MethHb (MethHb is >3%).** For the purposes of this study the site investigator is responsible for recording all AEs, regardless of their relationship to study intervention, for the period from randomisation until completion of each individual child's participation in the study.

This study is performed in infants and children undergoing high risk cardiac surgical procedures with death or high risk organ support such as ECLS or renal replacement therapy within the expected outcome. We will report all SAE including deaths and the investigators will give clinical recommendations if the death was unexpected and reason for further investigation by the DSMB.

Additional screening for adverse events will occur at the time of patient discharge from hospital.

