### 8.4 Serious adverse event reporting

Any SAE occurring in a study participant will be reported to the HREC within 24-72 hours of detection, in accordance with the safety reporting policy of the HREC. The HREC safety reporting form will be completed, signed and submitted by an investigator.

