#### *Safety outcomes*

Adverse drug reactions considered to be possibly, probably, or definitively related to the study treatment based on the judgement of the treating local physician, will be reported in supplementary material. Additionally, the proportion of patients with at least one adverse event will be compared between the two treatment groups using logistic regression as described above for secondary outcomes.

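### The SAP's first-surgery rule leaves adverse events at repeat study-gas exposures without a place in the planned by-arm safety analysis

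*Combined protocol and SAP*

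**What the plan says.** **Re-exposure.** Protocol 5.1.2 (the note after the exclusion criteria) states: "Previously enrolled and randomised patients will undergo the same treatment allocation for subsequent surgeries, unless parents opt out". Sections 5.3 and 6.1 repeat the rule. The reason given in 5.1.2 is that a possible additive protective effect of NO on neurodevelopment could be diluted by later bypass without it. The same note gives the expected frequency: "We expect that ca. 10% of all CPB cases <2 years may require subsequent CPB <2 years of age".

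**What is analysed.** Under Statistical analysis principles, the SAP says that children operated on more than once before their second birthday "will only have data related to their first surgery for which study consent was available analysed". It also says: "This analysis plan and the primary manuscript will only include analyses up to 28 days". The topics it defers to separate reports are delirium, costs, inflammatory markers and long-term outcomes. Datasets analysed puts adverse events in the same primary dataset as the outcomes.

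**Safety.** Under Safety outcomes, "the proportion of patients with at least one adverse event will be compared between the two treatment groups using logistic regression". No separate rule is given for later exposures. The SAP names two subgroups, age and physiology.

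**Collection and other channels.** Protocol 8.1 has the site record all adverse events "for the period from randomisation until completion of each individual" child's participation, although the same section defines an adverse event by an intraoperative and 48-hour postoperative window. Protocol 8.4 adds: "Any SAE occurring in a study participant will be reported to the HREC within 24-72 hours of detection". The SAP's interim analyses gave adverse event information to the DSMB, and its list of supplementary material includes an adverse event listing. Protocol 3.3 pre-plans a subgroup analysis of children with several bypass procedures.

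**The concern.** Restricting ventilator-free days and the other 28-day outcomes to the index operation is sound. The difficulty is that the restriction stands among the general principles and so reaches safety as well. Because allocation is kept at re-operation, the NO-arm children with later surgery are those with the highest cumulative exposure. The protocol justifies repeat dosing by a possible cumulative benefit, while the SAP has no matching summary of possible cumulative harm.

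Protocol 8.1 names three events specific to NO delivery: air embolism, severe hypotension during bypass and methaemoglobin above 3%. Each could arise at a second exposure as well as at the first. Under the plan as written, the published comparison would describe safety at a first operation, although the trial delivered the gas at later ones too.

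**Working it through.** **1. Where a later-surgery adverse event goes.** Take a NO-arm child with raised methaemoglobin at a second bypass operation some months after the first.

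| Place in the documents | Does it cover this event? |
|---|---|
| SAP, Statistical analysis principles | No: first-surgery data only, and a 28-day horizon |
| SAP, Safety outcomes | No exception to that rule |
| SAP, Table 2 (methaemoglobin rows) | Intervention arm only; the footnote covers several runs in one surgery, not later surgeries |
| SAP, Subgroup and sensitivity analyses | Age and physiology only |
| SAP, separately reported topics | Later adverse events not named |
| SAP, adverse event listing | Scope not stated; a listing gives no rates |
| Protocol 3.3, repeat-bypass subgroup | Adverse events not named; not carried into the SAP |
| Protocol 8.4 and DSMB review | May see the event; no published rate by arm |

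**2. Check of the sample size that supplies the denominator.** Inputs from protocol 11.2: effect 0.2 SD, 90% power, two-sided 5%, 10% withdrawals, 15% for non-normality. The 1:1 ratio is in the SAP's Randomisation section.

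- Base: n per arm = 2 × (1.960 + 1.282)² / 0.2² = 526 (rounded up).
- 526 × 1.15 / 0.9 = 673 per arm (1,346 in total).
- 526 × 1.10 × 1.15 = 666 per arm (1,332).
- 526 × 1.25 = 658 per arm (1,316).

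All three are within 2% of the plan's 1,320, so 660 per arm is usable.

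**3. Expected re-exposed children.** Inputs: the 10% from protocol 5.1.2; assumed equal share in each arm and no opt-outs.

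- All randomised: 0.10 × 660 = 66 in the NO arm, 132 in both arms.
- After 10% withdrawals: 0.10 × 594 = 59 in the NO arm, 118 in both arms.
- If the share were 5% to 15% (an assumption, since the documents give only the 10%): from 0.05 × 594 = 30 to 0.15 × 660 = 99 in the NO arm.

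**4. What those children could show.** With zero events among m children, the exact one-sided 95% upper bound is 1 − 0.05^(1/m).

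- m = 66: 4.4%.
- m = 59: 5.0%.
- m = 30: 9.5%; m = 99: 3.0%.

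The chance of at least one event among 66 is 1 − (1 − p)^66, which is 48% at a true rate of 1% and 97% at 5%. Power to detect 10% against 20% with 66 per arm is about 36%. The set can support description but not a formal test.

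**The case against.** A reader might infer that harm from repeat dosing is removed from every analysis and cannot surface anywhere. The documents do not support that.

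- Protocol 8.1 promises that all serious adverse events will be reported, 8.4 sends them to the ethics committee, the DSMB saw adverse event information, and a listing is planned. None of these is expressly limited to the first operation.
- The subgroup in protocol 3.3 is worded as including neurocognitive and functional outcome, which is not a closed list. The separate 12-month reports would also carry any effect of re-exposure before that visit.
- Re-operations after day 28 lie outside this SAP's horizon in any case, which is partly a decision about scope.
- A death or further ventilation after a second bypass within 28 days of the first CPB start would meet the outcome definitions in SAP appendix S2, although the first-surgery wording makes this ambiguous.

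These points stand and narrow the concern. They do not close it: individual reports and a listing of unstated scope are not rates by arm with a denominator.

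A second tempting reading is that eligibility is not checked again before a repeat exposure. That is unproven. Protocol 7.1 screens all cardiac surgical patients and does not exempt re-operations, while 5.1.2, 5.3 and 6.1 name only parental opt-out and the withdrawal section in 5.3 is permissive. The documents are unclear; they do not establish that no check takes place.

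Three further objections also stand. Whether second-surgery events are collected as trial data is not fully settled, because 8.1 combines a 48-hour definition with recording to the end of participation. The 10% refers to all bypass cases under two years, not to the enrolled cohort. And re-operated children are selected after randomisation by survival, need for surgery and opt-out, so a comparison by arm among them is not protected by randomisation.

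**Conclusion.** The point holds in this limited form: the SAP's general first-surgery rule, with no safety exception, gives adverse events at later study-gas exposures no place in the planned by-arm safety analysis, although the protocol continues the allocation at those operations. About 59 to 66 NO-arm children would be affected. If no event of a given kind occurred among them, the data would exclude a risk above about 4.4% to 5.0% (one-sided 95%), a statement that the plan as written does not provide for.

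The size rests on the protocol's 10% applying to the enrolled children, equal shares by arm, no opt-outs, and a count of children rather than exposures. The primary analysis is unaffected. The SAP should be changed because the gap follows from a stated rule and limits what the trial can report on the safety of repeat exposure.

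**What to change.** 1. In Statistical analysis principles, limit the first-surgery rule to the efficacy, process-of-care and physiological outcomes. Under Safety outcomes, state that the patient-level comparison refers to the first surgery.
2. Add a descriptive supplementary table of adverse events, and of methaemoglobin where recorded, at repeat study-gas exposures by randomised arm, with numbers of children and of exposures.
3. State that the adverse event listing covers later surgeries.
4. Say where the repeat-bypass subgroup of protocol 3.3 will be reported.

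Separately, protocol 5.1.2, 5.3 (including its withdrawal section), 6.1 and 7.1 must be reconciled on whether eligibility is checked before a repeat exposure, and the 48-hour adverse event definition in 8.1 must be reconciled with the recording period there and in 8.3.

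**Cost.** SAP wording and one table. No new patients are needed and the primary analysis does not change. If adverse events at later surgeries prove not to have been collected consistently, the table must say so. The estimates will be imprecise, exposures within a child are correlated, and re-operated children are a post-randomisation selection, so the table should carry no test and be labelled descriptive.

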## 2.2. Hypothesis and Aim

**Aims.** 1. To investigate in a double blind randomized controlled trial in children undergoing open heart surgery if NO exposure during CPB reduces the postoperative duration of invasive mechanical ventilation (defined as ventilator free days within 28 days post randomisation) compared to control.

2. To demonstrate that NO reduces the incidence of low cardiac output syndrome (LCOS), requirement for extracorporeal life support (ECLS), and 28-day mortality

2. To demonstrate that NO reduces the length of PICU stay and health care costs

3. To demonstrate that NO reduces the inflammatory response following CPB.

**Hypotheses.** Infants and children undergoing cardiac surgery on CPB exposed to gaseous nitric oxide (NO) have compared to controls, less myocardial injury and a reduced inflammatory response, leading to reduced incidence of LCOS. We hypothesize that lower LCOS will translate into reduced secondary organ failure and a reduced postoperative intensive care resource utilisation measured by length of mechanical ventilation, and will ultimately result in a reduction in mortality and health care costs.

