## **Outcome measures**

The definition and detail of calculation of outcome measures can be found in the Supplementary Appendix (Section S2), alongside the Stata scripts written to calculate these outcomes (available on GitHub (16)). Briefly, the outcomes are:

- Primary outcome measure: VFDs within 28 days from start of CPB
- Secondary outcome measures:

- Individual VFD components (i.e. duration of mechanical ventilation, death within 28 days after CPB start)
- Individual and components of composite measure of LCOS, and/or ECLS within 48 hours after CPB start and/or death within 28 days after CPB start;
- Length of PICU stay after CPB start;
- Length of hospital stay after CPB start;
- Process of care measures:
  - Treatment with ECLS within 48 hours after CPB start;
  - Duration of postoperative time spent with open chest including unplanned chest reopening after CPB start;
  - Treatment and duration of treatment using inhalational nitric oxide postoperatively after CPB start;
  - Treatment and duration of treatment of postoperative renal replacement therapy (includes peritoneal and continuous venous-venous haemodialysis) after CPB start;
- Physiological descriptors:
  - Postoperative troponin levels during the first 24 hours postoperatively;
  - Severity and duration of postoperative organ dysfunction; and
  - Postoperative acute kidney injury (AKI) and serum creatinine levels measured during the first 24 hours.

For the purposes of analysis and reporting, LCOS within 48 hours after CPB start, ECLS within 48 hours after CPB start, death within 28 days after CPB start and length of stay in PICU and hospital are classified as potentially patient-important secondary outcomes. The remaining secondary outcomes will be reported to describe patient physiology and processes of care only.

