| Blood products received in theatre                     |                    |                     |                     |
| Red blood cells (mL/kg) median (IQR)                   |                    |                     |                     |
| Whole blood (mL/kg) median (IQR)                       |                    |                     |                     |
| Platelets (mL/kg) median (IQR)                         |                    |                     |                     |
| Fresh frozen plasma (mL/kg) median (IQR)               |                    |                     |                     |
| Cryoprecipitate (mL/kg) median (IQR)                   |                    |                     |                     |
| Drug treatments received in theatre                    |                    |                     |                     |
| Intravenous steroids n (%)                             |                    |                     |                     |

|                                                                                                          |  |  |  |
|----------------------------------------------------------------------------------------------------------|--|--|--|
| Inhaled NO n (%)                                                                                  |  |  |  |
| Administration of study drug (nitric oxide)                                                       |  |  |  |
| Time from start of CPB to start of NO (min) mean (SD)/median (IQR)                                |  |  |  |
| Duration of NO on CPB (min) median (IQR)                                                          |  |  |  |
| Proportion of time spent on CPB with NO* mean (SD)/median (IQR)                                   |  |  |  |
| Change in methaemoglobin level (%) between start and post-CPB mean (SD)/median (IQR) ^ |  |  |  |
| Change in methaemoglobin level (%) between start and post-CPB >3% ^ n (%)              |  |  |  |

390     \* if multiple CPB runs during the same surgery, summarising every CPB run individually; ^ calculated as post-CPB methaemoglobin – pre-CPB

391     methaemoglobin

392     IQR interquartile range; CPB cardiopulmonary bypass; SD standard deviation; NO nitric oxide

393 Table 3. Primary and secondary outcomes per intention-to-treat analysis

394

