| Outcome                                                               | Standard Care
N= | Nitric
Oxide
N= | Unadjusted
p-value | Estimate of
Difference
(95% CI) | Adjusted
p-value |
|-----------------------------------------------------------------------|---------------------|-----------------------|-----------------------|---------------------------------------|---------------------|
| Primary Outcome                                                |                     |                       |                       |                                       |                     |
| Ventilator-free days median (IQR)                              |                     |                       |                       |                                       |                     |
| Secondary Outcomes                                             |                     |                       |                       |                                       |                     |
| Duration of invasive ventilation median (IQR)                  |                     |                       |                       |                                       |                     |
| Low cardiac output syndrome, need for ECLS or death n (%)      |                     |                       |                       |                                       |                     |
| Low cardiac output syndrome n (%)                              |                     |                       |                       |                                       |                     |
| ECLS n (%)                                                     |                     |                       |                       |                                       |                     |
| Death n (%)                                                    |                     |                       |                       |                                       |                     |
| Length of stay in PICU median (IQR)                            |                     |                       |                       |                                       |                     |
| Length of stay in hospital median (IQR)                        |                     |                       |                       |                                       |                     |

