### 411 *Secondary Outcomes*

412 The main secondary outcome is defined by a composite of presence of LCOS, extracorporeal life support (ECLS), or all-cause death.

- 413 • The presence of LCOS (21) will be calculated as a binary variable by evaluating the relevant data items at the following time-points: admission  
414 to PICU, and after six hours, 12 hours, 24 hours, and 48 hours post-PICU admission, or until the patient is discharged from PICU (whichever  
415 occurs first). Criteria for LCOS include a blood lactate level (arterial where available, if not then venous) >4 mmol/L and the presence of an  
416 oxygen extraction of greater than 35% ( $\text{SaO}_2\text{-ScvO}_2$  gradient >35%), or a high inotrope requirement operationalised as Vasoactive-Inotrope  
417 Score (VIS)  $\geq 15$  (22, 23). If these criteria are met for at least one of the above listed timepoints, the presence of LCOS is confirmed. If individual  
418 data items required for the calculation of LCOS are missing, then the patient will be assumed not to have had LCOS.

- ECLS post-CPB during the first 48 hours after CPB start.
- Mortality is defined as all-cause death within the first 28 days after CPB start.

Additional secondary outcomes include PICU and hospital length of stay, which will be measured from start time of CPB. In patients discharged alive from the PICU to the ward and readmitted within 72 hours the subsequent PICU admission duration will be added to the index admission. Length of stay (both PICU and hospital) will be censored at 28 days or when the patient was last alive, whichever occurs earlier. Patients who die during their PICU or hospital admission will be assigned the time to event.

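### SAP Table 3 puts two p-value columns over 22 secondary comparisons that the SAP says are exploratory and reported as estimates with CIs, and the named main secondary outcome has no inferential standing

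*Combined protocol and SAP*

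**What the plan says.** **Reporting rule.** SAP, Statistical analysis principles: "Statistical tests will be two-sided applying a statistical significance level of 0.05". The next sentence begins "As we are not correcting for multiplicity when comparing secondary or other outcomes" and continues "such results will be considered exploratory and will be reported as point estimates with 95% confidence intervals (CIs").

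**Methods text.** SAP, Primary outcome measure, plans p-values for ventilator-free days. SAP, Secondary outcome measures, plans odds ratios, hazard ratios and mean differences with 95% CIs and mentions no p-value.

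**Descriptive rows.** SAP, Outcome measures, classes low cardiac output syndrome (LCOS), ECLS, death and the two lengths of stay as potentially patient-important. It then says: "The remaining secondary outcomes will be reported to describe patient physiology and processes of care only".

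**Table shell.** "Table 3. Primary and secondary outcomes per intention-to-treat analysis" has an unadjusted p-value column, an estimate with 95% CI, and an adjusted p-value column. They head all rows, with no note limiting the p-values to the primary row. One of the rows is "Low cardiac output syndrome, need for ECLS or death".

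**Rank of the composite.** SAP Supplementary Appendix S2: "The main secondary outcome is defined by a composite of presence of LCOS, extracorporeal life support (ECLS), or all-cause death". Protocol section 2.2 has an aim "To demonstrate that NO reduces the incidence of low cardiac output syndrome (LCOS"), with ECLS and 28-day mortality listed beside it. No testing order or alpha allocation is given for any secondary outcome.

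**The concern.** There are two linked problems.

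First, the reporting rule and the table shell point in different directions. An analyst who fills in the shell will produce two p-values for each secondary comparison, including the rows that the SAP calls descriptive. An analyst who follows the principles and the methods text will leave those cells blank. In the main results table, a p-value below 0.05 on one of many uncorrected rows is easily read as a finding, which is what the principles try to prevent.

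Second, calling one secondary outcome the main one suggests that it carries more weight than the rest. Under the principles it carries none: whatever the result, it is exploratory. The trial may therefore give up a formal conclusion on LCOS, ECLS or death that it could have had without spending any alpha on the primary outcome.

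**Working it through.** **1. The plan's own figure.** The documents give no error rate for the secondary outcomes. The only related figure is the sample size (SAP, Sample size: 0.2 SD, 90% power, two-sided 5%, 10% withdrawals, 15% for non-normality). Per group, 2 × (1.960 + 1.282)² / 0.2² = 525.4, so 526. Adding 10% and 15% gives 526 × 1.25 = 657.5, in line with the stated 660 per group and 1,320 in total. This point does not affect that figure.

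**2. Row count in Table 3, below the primary row.**
- Secondary outcomes, 7: duration of ventilation, composite, LCOS, ECLS, death, PICU stay, hospital stay.
- Process of care, 5: open-chest time, inhaled nitric oxide (yes/no and duration), renal replacement (yes/no and duration).
- Physiological, 10: PELOD-2 at three times, troponin at two, creatinine at two, acute kidney injury at three.

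Total 7 + 5 + 10 = 22, leaving out the nine kidney-injury stage sub-rows. Two p-value columns make 44 cells.

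**3. Chance of at least one p<0.05 if there is no effect on any outcome** (one test per row at two-sided 0.05).
- Expected number of false positives: 22 × 0.05 = 1.1.
- Independent rows: 1 − 0.95²² = 0.68.
- Equally correlated normal test statistics: 0.57 at pairwise correlation 0.3, and 0.44 at 0.5.
- The 7 secondary outcomes alone, if independent: 1 − 0.95⁷ = 0.30.

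The correlations are assumptions; the documents give none.

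**4. What a test of the composite could deliver.** The SAP gives no event rate for the composite. The protocol background puts LCOS after bypass at about 25-40%, so control rates of 30% and 36% are assumed. With n = 660 × 0.9 = 594 per arm, power = Φ[(|p1 − p2| − 1.96·s0)/s1], where s0 uses the pooled rate and s1 the two separate rates.

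| Control vs nitric oxide (assumed) | s0 | s1 | Φ argument | Power |
|---|---|---|---|---|
| 36% vs 27% | 0.02695 | 0.02683 | 1.39 | 92% |
| 30% vs 22% | 0.02545 | 0.02535 | 1.19 | 88% |
| 30% vs 24% | 0.02576 | 0.02570 | 0.37 | 64% |

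This is the power of the composite test once the gate is open, taken on its own.

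**5. Effect of the gate.** The primary must succeed first. If the primary has its planned 90% power, the chance that both tests succeed lies between 0.90 + power − 1 and the smaller of the two powers, whatever their correlation: 82-90%, 78-88% and 54-64% for the three rows. If the true effect on ventilator-free days is below 0.2 SD, the chance is lower still.

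**6. Error control.** Testing the composite at 0.05 only after a primary p<0.05 holds the family-wise error for the two tests at 0.05. This sets aside the interim looks, for which the SAP (Interim analyses) makes no adjustment.

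**The case against.** The strongest reply is that the SAP is already open about this. It declares in advance that there is no correction and that the results are exploratory, and the error rates above matter only to someone who reads a single row as a confirmed effect. Taking out the p-values would not remove chance findings, since a 95% CI excludes the null about as often as p<0.05. Protocol section 11.1 prefers confidence intervals where possible but allows standard tests for secondary outcomes, so nominal p-values are not alien to the plan. Keeping the composite exploratory is also defensible, because the protocol itself says that LCOS has no accepted standard definition. All of this stands, and it limits the weight of the point. It does not settle which instruction the analyst should follow for Table 3.

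Four stronger readings are tempting, and the documents do not support them.
- That the SAP forbids p-values for secondary outcomes. It says how results will be reported; it does not say that nothing else may appear.
- That the protocol set out to demonstrate an effect on the composite. Section 2.2 lists LCOS, ECLS and mortality as separate items and uses the same verb for PICU stay and costs and for inflammation. The composite's rank comes from S2 alone, and the SAP's list of patient-important outcomes names its components, not the composite.
- That the table will probably show a false positive. The chance is above one half at correlations of 0 and 0.3 but below it at 0.5, and many rows are nested or repeated over time.
- That a test is planned for each kidney-injury stage. Those are count sub-rows under a shared header.

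**Conclusion.** The point holds as an inconsistency within the SAP together with a missed opportunity; it is not a hidden error. The principles and methods text describe secondary results as estimates with CIs, whereas the Table 3 shell provides p-value columns for all 22 secondary comparisons without a limiting note. The indicative chance of at least one nominally significant row under no effect is 44-68%, on assumed pairwise correlations from 0.5 down to 0.

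The composite is called the main secondary outcome but has no inferential status to match. A gated test would have useful power for larger assumed differences (88-92%) and modest power for a smaller one (64%), in each case before allowing for the gate. These figures rest on assumed event rates and on 594 evaluable patients per arm.

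The primary analysis and the sample size are unaffected. The change is worth making because it is cheap and alters what the trial may conclude about the composite.

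**What to change.** Before unblinding, and declared as a change to the SAP:

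1. In Table 3, limit both p-value columns to the primary row, and to the composite if it is to be tested. Leave the estimate and 95% CI in all other rows. Alternatively, keep the other p-values and label them nominal and uncorrected in a table note.
2. Name the one primary test that decides. The SAP plans both a p-value with the stratum- and site-adjusted quantile regression estimate and an unadjusted Mann-Whitney p-value. Then state: if that test has p<0.05, the composite is tested at two-sided 0.05; otherwise it is reported as exploratory. If the investigators prefer to keep the composite exploratory throughout, say so beside its description in S2.

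Optional, as preferences and not corrections: one ordinal estimate of kidney injury per time point with the stages left as counts, and no interaction p-values for secondary outcomes.

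The cost is a wording and table-shell edit. No primary alpha is used and N stays at 1,320. The other secondary rows lose, or have relabelled, p-values on which the SAP does not intend to rely.
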